**Weight-Based Administration of Study Medications (3-arm study)**

| **Weight (kg)** | **Amodiaquine (AQ)**  **200 mg tabs** | | | **Artesunate (AS)**  **50 mg tabs** | | | **Chloroquine (CQ)**  **250 mg tabs** | | | **SP** | | |
| --- | --- | --- | --- | --- | --- | --- | --- | --- | --- | --- | --- | --- |
| **SP (500mg/ 25mg)** | **Placebo** | |
|  | **Day 0** | **Day 1** | **Day 2** | **Day 0** | **Day 1** | **Day 2** | **Day 0** | **Day 1** | **Day 2** | **Day 0** | **Day 1** | **Day 2** |
| 5 | ¼ | ¼ | ¼ | ½ | ½ | ½ | ¼ | ¼ | ¼ | ¼ | ½ | ½ |
| 6 | ¼ | ¼ | ¼ | ½ | ½ | ½ | ½ | ¼ | ¼ | ¼ | ½ | ½ |
| 7 | ¼ | ¼ | ¼ | ½ | ½ | ½ | ½ | ½ | ¼ | ¼ | ½ | ½ |
| 8 | ½ | ¼ | ¼ | ¾ | ¾ | ¾ | ½ | ½ | ½ | ½ | ¾ | ¾ |
| 9 | ½ | ¼ | ¼ | ¾ | ¾ | ¾ | ½ | ½ | ½ | ½ | ¾ | ¾ |
| 10 | ½ | ½ | ¼ | ¾ | ¾ | ¾ | ¾ | ½ | ½ | ½ | ¾ | ¾ |
| 11 | ½ | ½ | ¼ | 1 | 1 | 1 | ¾ | ¾ | ½ | ½ | 1 | 1 |
| 12 | ½ | ½ | ½ | 1 | 1 | 1 | ¾ | ¾ | ½ | ½ | 1 | 1 |
| 13 | ½ | ½ | ½ | 1 | 1 | 1 | 1 | ¾ | ½ | ¾ | 1 | 1 |
| 14 | ¾ | ½ | ½ | 1 ¼ | 1 ¼ | 1 ¼ | 1 | 1 | ½ | ¾ | 1 ¼ | 1 ¼ |
| 15 | ¾ | ½ | ½ | 1 ¼ | 1 ¼ | 1 ¼ | 1 | 1 | ½ | ¾ | 1 ¼ | 1 ¼ |
| 16 | ¾ | ¾ | ½ | 1 ¼ | 1 ¼ | 1 ¼ | 1 | 1 | ¾ | ¾ | 1 ¼ | 1 ¼ |
| 17 | ¾ | ¾ | ½ | 1 ½ | 1 ½ | 1 ½ | 1 | 1 | 1 | ¾ | 1 ½ | 1 ½ |
| 18 | 1 | ¾ | ½ | 1 ½ | 1 ½ | 1 ½ | 1 | 1 | 1 | ¾ | 1 ½ | 1 ½ |
| 19 | 1 | ¾ | ½ | 1 ½ | 1 ½ | 1 ½ | 1 ¼ | 1 | 1 | 1 | 1 ½ | 1 ½ |
| 20 | 1 | 1 | ½ | 1 ¾ | 1 ¾ | 1 ¾ | 1 ¼ | 1 ¼ | 1 | 1 | 1 ¾ | 1 ¾ |
| 21 | 1 | 1 | ½ | 1 ¾ | 1 ¾ | 1 ¾ | 1 ¼ | 1 ¼ | 1 | 1 | 1 ¾ | 1 ¾ |
| 22 | 1 ¼ | 1 | ½ | 1 ¾ | 1 ¾ | 1 ¾ | 1 ½ | 1 ½ | ¾ | 1 | 1 ¾ | 1 ¾ |
| 23 | 1 ¼ | 1 | ½ | 2 | 2 | 2 | 1 ½ | 1 ½ | 1 | 1 ¼ | 2 | 2 |
| 24 | 1 ¼ | 1 ¼ | ½ | 2 | 2 | 2 | 1 ½ | 1 ½ | 1 | 1 ¼ | 2 | 2 |
| 25 | 1 ¼ | 1 ¼ | ½ | 2 | 2 | 2 | 1 ½ | 1 ½ | 1 ¼ | 1 ¼ | 2 | 2 |
| 26-27 | 1 ¼ | 1 | 1 | 2 ¼ | 2 ¼ | 2 ¼ | 1 ½ | 1 ½ | 1 ¼ | 1 ½ | 2 ¼ | 2 ¼ |
| 28 | 1 ¼ | 1 ¼ | 1 | 2 ¼ | 2 ¼ | 2 ¼ | 2 | 1 ½ | 1 ½ | 1 ½ | 2 ¼ | 2 ¼ |
| 29-31 | 1 ¼ | 1 ¼ | 1 | 2 ½ | 2 ½ | 2 ½ | 2 | 2 | 1 | 1 ½ | 2 ½ | 2 ½ |
| 32 | 1 ½ | 1 ½ | 1 | 2 ½ | 2 ½ | 2 ½ | 2 | 2 | 1 ½ | 1 ½ | 2 ½ | 2 ½ |
| 33 | 1 ½ | 1 ½ | 1 | 2 ¾ | 2 ¾ | 2 ¾ | 2 | 2 | 1 ½ | 1 ½ | 2 ¾ | 2 ¾ |
| 34-35 | 1 ½ | 1 ½ | 1 ¼ | 2 ¾ | 2 ¾ | 2 ¾ | 2 | 2 | 2 | 1 ½ | 2 ¾ | 2 ¾ |
| 36-37 | 1 ½ | 1 ½ | 1 ¼ | 3 | 3 | 3 | 2 | 2 | 2 | 1 ½ | 3 | 3 |
| 38 | 2 | 1 ½ | 1 ¼ | 3 | 3 | 3 | 2 | 2 | 2 | 2 | 3 | 3 |
| 39 | 2 | 1 ½ | 1 ¼ | 3 ¼ | 3 ¼ | 3 ¼ | 2 | 2 | 2 | 2 | 3 ¼ | 3 ¼ |
| 40-43 | 2 | 2 | 1 | 3 ¼ | 3 ¼ | 3 ¼ | 2 ½ | 2 ½ | 1 ½ | 2 | 3 ¼ | 3 ¼ |
| 44-47 | 2 | 2 | 1 ½ | 3 ½ | 3 ½ | 3 ½ | 3 | 3 | 2 | 2 ½ | 3 ½ | 3 ½ |
| 48-49 | 2 | 2 | 2 | 3 ¾ | 3 ¾ | 3 ¾ | 3 | 3 | 2 | 2 ½ | 3 ¾ | 3 ¾ |
| 50-59 | 2 ½ | 2 | 2 | 4 | 4 | 4 | 4 | 4 | 2 | 2 ¾ | 4 | 4 |
| >60 | 3 | 3 | 1 ½ | 5 | 5 | 5 | 4 | 4 | 2 | 3 | 5 | 5 |

**Appendix 5. Guidelines for Grading Patient Symptoms**

|  | **Grade 1**  **MILD** | **Grade 2**  **MODERATE** | **Grade 3**  **SEVERE** | **Grade 4**  **LIFE THREATENING** |
| --- | --- | --- | --- | --- |
| **Subjective fever in the past 24 h** | N/A | Present (Yes) | N/A | N/A |
| **Convulsion** | N/A | N/A | Localized or generalized seizure | Status epilepticus |
| **Headache*** | Mild, no therapy required | Transient, moderate; therapy required | Severe; responds to initial narcotic therapy | Intractable; requires repeated narcotic therapy |
| **Anorexia** | Decreased appetite, but still taking solid food | Decreased appetite, avoiding solid food | Refusing to breast feed, appetite very decreased, no solids or liquids taken (< 2 years < 12 hr; > 2 years < 24 hr) | Refusing to breast feed, appetite very decreased, no solids or liquids taken (< 2 years < 12 hr; > 2 years < 24 hr) |
| **Nausea*** | Mild discomfort; maintains reasonable intake | Moderate discomfort; intake decreased significantly; some activity limited | Severe discomfort; no significant intake; activities limited | Minimal fluid intake |
| **Vomiting** | Transient emesis | Occasional or moderate vomiting | Orthostatic hypotension or IV fluids required | Hypotensive shock or hospitalization required for IV fluid therapy |
| **Abdominal pain*** | Mild | Moderate – no treatment needed | Moderate to severe – treatment needed | Severe – hospitalized for treatment |
| **Diarrhea** | Transient 3-4 loose stools/day | 5-7 loose stools/day | Orthostatic hypotension or > 7 loose stools/day or IV fluids required | Hypotensive shock or hospitalization for IV fluid therapy required |
| **Cough** | Transient – no treatment required | Continuous, requires treatment | Uncontrolled | Cyanosis, stridor, severe shortness of breath |
| **Pruritis** | Pruritis without rash | Pruritic rash, pruritis without rash that disturbs sleep | Mild urticaria | Severe urticaria, anaphylaxis, angioedema |
| **Tinnitus*** | Mild ringing or roaring sound | Moderate ringing or roaring sound | Severe ringing or roaring sound with associated hearing loss | N/A |
| **Behavioural changes** | Mild difficulty concentrating; mild confusion or agitation; activities of daily living unaffected; no treatment | Moderate confusion or agitation; some limitation of activities of daily living; minimal treatment | Severe confusion or agitation; Needs assistance for activities of daily living; therapy required | Toxic psychosis; hospitalization required |
| **“Flu”**  **(viral URI)** | Mild nasal congestion, mild rhinorrhea, no cough | Moderate nasal congestion, moderate rhinorrhea, cough present | N/A (if severe, classify individual symptoms) | N/A (if life-threatening, classify individual symptoms) |
| *** Assess only in children > 3 years of age. Answer N/A for younger children and those unable to answer.** | | | | |

###### † Reference – Based on WHO Toxicity Grading Scale for Determining the Severity of Adverse Events

###### APPENDIX 6. Guidelines for Grading Examination Findings

###### Table A. Guidelines for Physical Examination

| **Dehydration** | Assess skin touch and turgor, mucous membranes, eyes, crying, fontanelle, pulse, urine output |
| --- | --- |
| **Facial edema** | Assess for swelling of eyes, face, mouth |
| **Jaundice** | Assess for yellowing of the sclera. Also evaluate the palpepral conjunctiva, lips, and skin. |
| **Chest** | Observe the rate, rhythm, depth, and effort of breathing. Check the patient’s colour for cyanosis.  The maximum acceptable respiratory rate by age: **< 2 months = 60, 2-12 months = 50, 1-5 years = 40, above 5 years = 30.**  Inspect the neck for the position of the trachea, for supraclavicular retractions, and for contraction of the sternomastoid or other accessory muscles during inspiration.  Auscultate the anterior and posterior chest for normal breath sounds and any adventitious sounds (crackles or rales, wheezes, and rhonchi). *Crackles are intermittent, non-musical, fine or coarse sounds that may be due to abnormalities of the lungs (pneumonia, fibrosis, early congestive heart failure) or airways (bronchitis or bronchiectasis). Wheezes are high-pitched and result from narrowed airways. Rhonchi are relatively low-pitched and suggest secretions in large airways.*  If abnormalities are identified, evaluate for transmitted voice sounds. In addition, palpate the chest to assess for tactile fremitus, and percuss the chest to assess for areas of dullness*. Normal, air-filled lungs emit predominantly vesicular breath sounds, transmit voice sounds poorly with “ee” = “ee”, and have no tactile fremitus. Airless lung, as in lobar pneumonia, emits bronchial breath sounds, transmits spoken words clearly with “ee” = “aay” (egophany), and has an increase in tactile fremitus.* |
| **Abdomen** | Inspect and ausculate the abdomen. Listen for bowel sounds in the abdomen before palpating it. Palpate the abdomen in all 4 quadrants lightly and then deeply. Assess the size of the liver and spleen. To assess for peritoneal inflammation, look for localised and rebound tenderness, and voluntary or involuntary rigidity. |
| **Skin** | Inspect the skin for colour, turgor, moisture, and lesions. If lesions are present, note their location and distribution (diffuse or localised), arrangement (linear, clustered, annular, dermatomal), type (macules, papules, vesicles) and colour. |
| **Hearing** | In children < 4 years, test hearing by shaking a rattle or crinkling paper from behind the head of the child on the right and left. Note child’s reaction to the noise – inspecting for a startle, or turning of the head toward the direction of the noise.  In children > 4 years of age, estimate hearing by testing one ear at a time. Ask the patient to occlude one ear with a finger or, better still, occlude it yourself. Gently rub your thumb and index finger together within 2 inches or 5 cm from the patient’s unoccluded ear and assess if the patient is able to hear the noise.  In children of all ages, perform a full otoscopic exam if these screening methods reveal any diminunition of hearing. In patients > 4 years of age only, attempt to assess for conductive and sensorineural hearing loss, using the tuning fork. Set the fork into light vibration by tapping it. Place the base of the lightly vibrating tuning fork firmly on top of the patient’s head or midforehead and test for lateralization (Weber test). Ask where the patient hears it: on one or both sides. Normally, the sound is heard in the midline or equally in both ears. If nothing is heard, try again, pressing the fork more firmly on the head. In unilateral conductive hearing loss, sound is heard in (lateralized to) the impaired ear. Visible explanations include acute otitis media, perforation of the eardrum, and obstruction of the ear canal, as by cerumen. In unilateral sensorineural hearing loss, sound is heard in the good ear.  Next, to compare air conduction (AC) and bone conduction (BC) perform the Rinne test. Place the base of lightly vibrating tuning fork on the mastoid bone, behind the ear and level with the canal. When the patient can no longer hear the sound, quickly place the fork close to the ear canal and ascertain whether the sound can be heard again. Hear the “U” of the fork should face forward, thus maximising its sound for the patient*. Normally, the sound is heard longer through air than through bone (AC>BC). In conductive hearing loss, sound is heard through bone as long as or longer than it is through air (BC=AC or BC>AC). In sensorineural hearing loss, sound is heard longer through air (AC>BC).* |
| **Nystagmus** | Assess the extraocular movements in children of all ages by moving a torch or brightly coloured object in a circle, looking for conjugate movements of the eyes in each directions, or any deviation from normal and for nystagmus, a fine rhythmic oscillation of the eyes, analogous to a tremor in other parts of the body. *A few beats of nystagmus on extreme lateral gaze are within normal limits. If you see it, bring your finger in to within the field of binocular vision and look again*.  *The causes of nystagmus are multiple, including impairment of vision in early life, disorders of the labyrinth and the cerebellar system, and drug toxicity. Nystagmus occurs normally when a person watches a rapidly moving object. Nystagmus usually has both fast and slow movements, but is defined by its fast phase. For example, if the eyes jerk quickly to the patient’s left and drift back slowly to the right, the patient is said to have nystagmus to the left. The movements of nystagmus may occur in one or more planes (i.e. horizontal, vertical, or rotatory). It is the plane of the movements, not the direction of the gaze that defines this variable.* |
| **Tablet test** | For children > 9 months of age, ask the patient to pick a tablet (or equivalent object) up off a flat surface using the thumb and index finger of their dominant hand*. This tests for co-ordination of the upper extremity assessing the function of the motor system, cerebellar system, vestibular system (for coordinating eye and body movements) and the sensory system, for position sense. When testing small children, be aware that they will likely attempt to put the object into their mouth.* |
| **Heel-toe** | For patients > 4 years of age, asks the patient to walk heel-to-toe in a straight line – a pattern called tandem walking. If the patient is unable to perform this, ask them to walk across the room normally, and/or to walk on their toes and then on the heels, to further assess gait pattern. A gait that lacks coordination in instability is called ataxic and may be due to cerebellar disease or loss of position sense.  For children 2-4 years of age, assess gait by having them walk in a straight line. |
| **Romberg** | This should be performed in children > 4 years and is mainly a test of position sense. The patient should first stand with feet together and eyes open and then close both eyes for 20 to 30 seconds without support. Note the patient’s ability to maintain an upright posture. To test for pronator drift, have the patient stand for 20 to 30 seconds with both arms straightforward, palms up, and with eyes closed. A person who cannot stand may be tested for pronator drift in the sitting position. In either case, a normal person can hold this arm position well. Now, instructing the patient to keep the arms up and eyes shut, tap the arms briskly downward. The arms normally return smoothly to the horizontal position. This response requires muscular strength, coordination, and a good sense of position.  In ataxia due to loss of position sense, vision compensates for the sensory loss. The patient stands fairly well with eyes open, but loses balance when they are closed, a **positive Romberg sign**. In cerebellar ataxia, the patient has difficulty standing with feet together whether the eyes are open or closed. |

**Table B. Grading Physical Examination Findings**

|  | **Grade 1**  **MILD** | **Grade 2**  **MODERATE** | **Grade 3**  **SEVERE** | **Grade 4**  **LIFE-THREATENING** |
| --- | --- | --- | --- | --- |
| **Dehydration*** | Normal skin turgor and touch, moist mucous membranes, tears present, eyes normal, fontanelle flat, CNS – consolable, pulse regular, urine output normal | Skin dry with + tenting, dry mucous membranes, eyes deep set, decreased tears, fontanelle soft, CNS – irritable, pulse slightly increased, urine output decreased | Skin clammy with lack of turgor, parched / cracked mucous membranes, sunken eyes, no tears, sunken fontanelle, CNS – lethargic, pusle increased, no urine output | |
| **Temperature* (Axillary)** | 37.5-37.9C | 38.0-39.5C | > 39.5C | Sustained fever, equal or greater than 40.0C for longer than 5 days |
| **Jaundice** | Slight yellowing of sclera and conjunctiva | Moderate yellowing of sclera and conjunctiva, yellowing of mucous membranes | Severe yellowing of sclera and conjunctiva, yellowing of skin | N/A |
| **Chest** | Mildly increased RR (for age, temperature), transient or localised adventitious sounds | Moderately increased RR, diffuse or persistent adventitious sounds | Rapid RR (< 2 months > 60, 2-12 months > 50, 1-5 years > 40, adults > 30)*nasal flaring, retractions | Cyanosis |
| **Abdomen** | Normal bowel sounds, mild localised tenderness, and/or liver palpable 2-4 cm below the right costal margin (RCM), and/or spleen palpable, and/or umbilical hernia present | Normal or mildly abnormal bowel sounds, moderate or diffuse tenderness; and/or mild to moderately enlarged liver (4-6 cm below the RCM) and/or spleen palpable up to half-way between umbilicus and symphysis pubis | Severely abnormal bowel sounds, severe tenderness to palpation. Evidence of peritoneal irritation and/or significant enlargement of liver (> 6 cm below the RCM) and/or spleen palpable beyond half-way between umbilicus and symphysis pubis | Absent bowel sounds. Involuntary rigidity |
| **Skin†** | Localised rash, erythema, or pruritis | Diffuse, maculopapular rash, dry desquamation | Vesiculation, moist desquamation, or ulceration | Exfoliative dermatitis, mucous membrane involvement or erythema multiforme or suspected Stevens-Johnson or necrosis requiring surgery |

* Reference – The Harriet Lane Handbook, 15th edition, 2000

† Reference – WHO Toxicity Grading Scale for Determining the Severity of Adverse Events

|  | **Grade 1**  **MILD** | **Grade 2**  **MODERATE** | **Grade 3**  **SEVERE** | **Grade 4**  **LIFE-THREATENING** |
| --- | --- | --- | --- | --- |
| **Hearing** | *< 4 years: N/A*  > 4 years: Decreased hearing in one ear | *< 4 years: N/A*  > 4 years: Decreased hearing in both ears or severe impairment in one ear | *< 4 years: Any evidence of hearing impairment*  > 4 years: Severe impairment in both ears | N/A |
| **Nystagmus** | 3 or fewer beats of lateral nystagmus | More than 3 beats of lateral nystagmus | Sustained lateral nystagmus, any vertical or rotary nystagmus | N/A |
| **Tablet test** | Difficulty grasping tablet but able to pick up | Unable to pick up tablet without dropping | Unable to grasp tablet | N/A |
| **Heel-toe** | 2-4 years: Able to take at least 5 steps  > 4 years: Able to take at least 5 tandem steps | 2-4 years: Unable to take 5 steps  > 4 years: Unable to take 5 tandem steps | *2-4 years: Unable to walk*  > 4 years: Unable to perform tandem walk | N/A |
| **Romberg** | > 4 years: Unable to stand for 30 seconds with eyes closed | > 4 years: Unable to stand for 15 seconds with eyes closed | > 4 years: Unable to stand with feet together with eyes open or closed | N/A |
| **Clinical symptoms / sign** *(not otherwise specified)* | No therapy; monitor condition | May require minimal intervention and monitoring | Requires medical care and possible hospitalization | Requires active medical intervention, hospitalization, or hospice care |

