**7.2.3 Reporting of adverse events:**

For each possible adverse event identified and graded as moderate, severe or life threatening, an adverse event report form will be completed (Appendix 15). An adverse event report form will not be completed for events classified as mild as these symptoms are common and difficult to distinguish from signs and symptoms due to malaria (however, mild AEs will still be included in the analysis). The following information will be recorded for all adverse experiences that are reported:

1. Description of event
2. Date of event onset
3. Date event reported
4. Maximum severity of the event
5. Maximum suspected relationship of the event to study medication
6. Is the event serious?
7. Initials of the person reporting the event
8. Was the event episodic or intermittent in nature?
9. Outcome
10. Date event resolved

Serious adverse events occurring in the trial shall be reported to the core facility by telecommunication within 24 hours. All information submitted by the surveillance sites will be collected at the Kampala core facility and reported to the Ugandan National Drug Authority and MoH.

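### Five rows of the adverse event grading tables do not separate adjacent grades: normal from mild, acceptable from severe respiratory rate, and severe from life-threatening anorexia

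*Protocol*

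**What the plan says.** The clinical record forms (Appendix 15) score each examination item from 0 to 4, with 0 for normal and 1 for a mild abnormality. The content of Grades 1 to 4 is set in Appendix 5 (symptoms) and in Appendix 6, Table B (examination findings). Table A of Appendix 6 tells the clinician how to examine and what is normal.

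- **Dehydration, Grade 1:** "Normal skin turgor and touch, moist mucous membranes, tears present, eyes normal, fontanelle flat", followed by a consolable child, a regular pulse and normal urine output.
- **Heel-toe, Grade 1, over 4 years:** "Able to take at least 5 tandem steps". The 2-4 year version is the same with ordinary steps.
- **Nystagmus:** Table A says "A few beats of nystagmus on extreme lateral gaze are within normal limits". Table B Grade 1 is "3 or fewer beats of lateral nystagmus".
- **Chest:** Table A lists "The maximum acceptable respiratory rate by age" as 60, 50, 40 and 30. Table B Grade 3 reads "Rapid RR (< 2 months > 60, 2-12 months > 50, 1-5 years > 40, adults > 30", then adds nasal flaring and retractions. Grades 1 and 2 refer to mild and moderate increases in rate without numbers, or to adventitious sounds.
- **Anorexia, Grades 3 and 4:** both cells begin "Refusing to breast feed, appetite very decreased, no solids or liquids taken" and end with the same age and duration limits.

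Section 7.2.2 defines an AE as an untoward sign or symptom that is new or has risen in severity since the previous record. Section 7.2.3 requires a report form from moderate upwards and says of the rest: "however, mild AEs will still be included in the analysis". Section 4.2.2 makes AE incidence by severity, and by specific sign or symptom, secondary outcomes.

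**The concern.** The grade does two jobs here. A rise in grade is what makes a finding an AE, and the grade decides the severity line in which the event is counted. A row that does not separate two neighbouring grades can therefore create an event or put a real one in the wrong place.

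Where normal and Grade 1 overlap, an unchanged healthy child can be scored 0 at one visit and 1 at the next, and the change meets the AE definition. Where Grade 3 starts at the acceptable limit, a small rise in respiratory rate can enter the reports as a severe AE. Where Grades 3 and 4 are the same, the choice between severe and life-threatening is left to the individual clinician.

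Later repair would be unreliable. The record form has one graded chest item and no field for the respiratory rate itself, so regrading would depend on the free-text description of abnormal findings.

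**Working it through.** The protocol gives no figure on this point to reproduce, so the check sets the cells side by side.

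**1. Normal against Grade 1.**
- The dehydration Grade 1 cell has eight descriptors: skin turgor and touch, mucous membranes, tears, eyes, fontanelle, consolability, pulse and urine output. All eight are given in their normal state, so the number of abnormal descriptors is 0 of 8. A well child satisfies both code 0 on the form and Grade 1 in Table B.
- Heel-toe Grade 1 states a success. Grade 2 is failing to take five steps. No wording places full, steady performance in Grade 0.
- For nystagmus, a few beats at extreme gaze are normal, while three or fewer lateral beats are Grade 1 with no mention of gaze position. The two overlap for end-gaze beats.

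**2. Respiratory rate.** Gap = Table B Grade 3 cut-off minus Table A acceptable maximum, reading adults in Table B as above 5 years in Table A:

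| Age band | Table A maximum | Table B Grade 3 | Gap (breaths/min) |
| --- | --- | --- | --- |
| under 2 months | 60 | above 60 | 60 - 60 = 0 |
| 2-12 months | 50 | above 50 | 50 - 50 = 0 |
| 1-5 years | 40 | above 40 | 40 - 40 = 0 |
| above 5 years / adults | 30 | above 30 | 30 - 30 = 0 |

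No rate above the acceptable maximum is left for Grades 1 and 2. A 3-year-old at 40/min is at the limit, and at 41/min already meets the Grade 3 rate criterion.

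**3. Anorexia.** The text of the Grade 3 and Grade 4 cells is identical, including the duration limits. No rule in the row separates the two grades.

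**Extent.** Appendix 5 has 13 rows, of which 1 is affected (anorexia). Table B has 11 named rows, of which 4 are affected (dehydration, chest, nystagmus, heel-toe). That is 5 of 24, or about 21%. The neurological examination is scheduled only in the three-arm study, on Day 0 and then on Days 7, 14, 21 and 28. Heel-toe and nystagmus thus have four scheduled follow-up gradings there and none in the two-arm study, where three rows remain affected.

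**The case against.** Several points on the other side have force.

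- **Most of the scale works.** The 0-4 range is stated consistently, and rows such as jaundice, skin, vomiting, diarrhoea, headache, hearing and Romberg run in order. AEs are also analysed by individual sign or symptom, which keeps a faulty row from contaminating the others. This stands and limits the point to the rows named.
- **Nystagmus is partly handled.** Table A tells the examiner who sees end-gaze beats to look again within the field of binocular vision. This stands; the overlap is weak, and Table B only needs to carry the qualification.
- **Heel-toe could mean an abnormal gait that still manages five steps**, as the tablet-test row does for grasping. That is plausible, but the tablet row states the difficulty and the heel-toe row does not.
- **Chest Grades 1 and 2 remain reachable** through adventitious sounds, or through a rate raised for age and temperature yet below the maximum. The first stands. The second is possible, but the text does not say so. It is also unclear whether rate alone, or rate with distress signs, makes Grade 3, because the punctuation joining them is broken.
- **The anorexia limits may have suffered in text extraction.** Comparison signs elsewhere look degraded: the reporting threshold prints as above grade 2, although a grade 2 event is given as an example. If the source file shows different limits in the two cells, that element falls away.
- **Grading is blinded and the tables are common to all arms.** This stands. Misgrading should be largely non-differential, and the normal-versus-mild faults affect only mild counts.

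A reader might infer that a Grade 4 anorexia score makes the event serious. Appendix 10 does not support that: it says seriousness depends on outcome or action taken and is not directly tied to severity.

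**Conclusion.** The fault is real and limited to five rows. It is clear for dehydration, for respiratory rate and, subject to a check of the source file, for anorexia. It is a matter of loose wording for heel-toe, and weak for nystagmus. The likely consequences are spurious mild AEs in the first group of rows and events placed at the wrong severity in the chest and anorexia rows. A finding scored Grade 1 consistently from Day 0 produces no AE, so spurious events need a change in scoring between visits.

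A reader might go further and conclude that the whole scale has the wrong range, or that AE incidence by grade cannot be interpreted. The documents do not support either, because the range is consistent and most rows are distinct. Nor can a loss of power be stated: the protocol gives no expected AE rates or misgrading rates, and its sample size rests on clinical failure at 28 days, not on any safety comparison.

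The conclusion assumes that adults in Table B means above 5 years, and that the anorexia cells are identical in the source file as they are in the text at hand.

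**What to change.** Before grading starts in the pilot, amend five rows:

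1. **Dehydration:** move the all-normal description to Grade 0 and word Grade 1 as a stated abnormality.
2. **Heel-toe:** place full performance in Grade 0 and say what is abnormal in Grade 1, for both age groups.
3. **Nystagmus:** state in Table B that end-gaze beats within normal limits are Grade 0.
4. **Chest:** reconcile the respiratory-rate limits of Tables A and B so that Grades 1, 2 and 3 are distinct, use the same age bands in both, and state whether rate alone or rate with distress signs defines Grade 3.
5. **Anorexia:** make Grades 3 and 4 mutually exclusive.

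Check each cell against the toxicity scale and the handbook that the appendices cite. The cost is the editing of five rows and a mention in the staff training already planned under section 9.2. No new assessments or patients are needed.

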### 7.2.2. Identification of adverse events:

At each follow-up visit (days 1, 2, 3, 7, 14, 21, 28, and any unscheduled day), study clinicians will assess patients according to a standardized clinical record form (Appendix 14). All signs and symptoms present will be graded as mild, moderate, severe, or life threatening according to examination guidelines (Appendix 6). An AE will be defined as a sign or symptom of untoward medical occurrence arising or increasing in severity compared to the previous day’s record.

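### Appendix 6 lets the eyes-closed Romberg stand end at 20 to 30 seconds but sets Grade 1 at 30 seconds, so for some patients Grade 0 or 1 can depend on when the examiner stops

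*Protocol*

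**What the plan says.** Appendix 6 of the protocol holds both the instructions for the examination and the scale for grading it.

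- **Table A (how to test).** The patient stands with feet together and eyes open, and must "then close both eyes for 20 to 30 seconds without support". The test is for children over 4 years.
- **Table B (how to grade).** Grade 1 is "Unable to stand for 30 seconds with eyes closed" and Grade 2 is "Unable to stand for 15 seconds with eyes closed". Grade 3 is inability to stand with feet together at all, eyes open or closed.
- **When it is done.** The follow-up schedule in Section 7.1 limits the neurologic exam to the three-arm study, on Days 0, 7, 14, 21 and 28, and on extra days as indicated. The three-arm clinical record form has one Romberg cell per visit (item 40).
- **How a change becomes an adverse event.** Section 7.2.2 states: "An AE will be defined as a sign or symptom of untoward medical occurrence arising or increasing in severity compared to the previous day’s record".
- **What happens to mild events.** Section 7.2.3 states: "An adverse event report form will not be completed for events classified as mild". It adds that "mild AEs will still be included in the analysis". Section 4.2.2 compares the arms on the proportion of patients with any adverse event, mild ones included, and on adverse events by specific sign or symptom.

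Nothing in the protocol fixes the eyes-closed stand at 30 seconds or says that Table B overrides the range in Table A.

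**The concern.** The longest stand that Table A permits equals the limit for Grade 1, and every shorter permitted stand falls below it. An examiner who stops a steady patient at 20 seconds has followed Table A, yet has not observed what Table B needs in order to call the result normal. The natural entry is 0. Another examiner, or the same one a week later, may run to 30 seconds, see the patient sway at 25, and enter 1. The patient has not changed, but the record now shows a sign arising since the previous exam, which is an adverse event under Section 7.2.2.

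At stake is a small part of the safety comparison. The neurologic exam belongs to the three-arm study, the design that adds artesunate, and Section 10.2 notes that neurotoxicity of that drug has been reported in animals. A Grade 1 sign whose value depends partly on how long the examiner waits is a weaker measure there than it need be.

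**Working it through.** The plan states no figure to reproduce on this point. The check sets the two tables against each other and follows a Grade 1 finding through the adverse event rules.

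**Step 1: which patients are affected.** Let t be the time for which a patient could stand with eyes closed, and s the time at which the examiner stops, with s anywhere from 20 to 30 seconds (Table A). A loss of balance is seen only if t is less than s. Applying the 30- and 15-second limits of Table B:

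| True time t | Test stopped at 20 s | Test run to 30 s | Does the grade depend on s? |
|---|---|---|---|
| under 15 s | Grade 2 or worse | Grade 2 or worse | No |
| 15 to under 20 s | Grade 1 | Grade 1 | No |
| 20 to under 30 s | still standing, entered as 0 | Grade 1 | **Yes** |
| 30 s or more | 0 | 0 | No |

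The ambiguous window is 30 − 20 = 10 seconds wide. The Grade 2 limit of 15 seconds lies below the 20-second minimum, so Grade 2 is assigned alike at any permitted duration. Grade 3 does not depend on duration.

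**Step 2: what the window does to the adverse event record.** I take the previous record for this sign to be the previous neurologic exam. Five scheduled exams then give 5 − 1 = 4 scheduled comparisons. For a patient with a constant t of 25 seconds:

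- 20 s then 30 s: grades 0 then 1, a spurious new mild adverse event.
- 30 s then 20 s: grades 1 then 0, no adverse event.
- 20 s both times: 0 and 0, no adverse event, although the patient meets the Grade 1 criterion.
- 30 s both times: 1 and 1, no change and no adverse event.

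For a patient who truly worsens from 30 seconds or more to 25, a later test stopped at 20 seconds gives 0 then 0, so a true new Grade 1 finding is missed. The error therefore runs in both directions.

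**Step 3: where it can surface.** A 0-to-1 change needs no report form under Section 7.2.3. It stays on the clinical record form and enters the analysis of mild events, and so the any-AE and by-sign outcomes of Section 4.2.2. No efficacy outcome uses it.

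**Step 4: can a trial-level rate be given?** It would need the share of patients over 4 years with t between 20 and 30 seconds, the spread of stop times, and how consistent each examiner is across visits. The protocol gives none of these, so no rate follows.

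**Step 5: after the fix.** With every test run to 30 seconds, s equals the Grade 1 limit. A patient with constant t then receives the same grade at each visit, and timing alone produces no 0-to-1 change.

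**The case against.** The strongest reply is that the two tables can be followed together. Thirty seconds lies inside the range in Table A, grades come from Table B, and Section 7.2.2 sends the examiner to Appendix 6, which holds both. An examiner who runs to 30 seconds satisfies everything, and staff are trained and tested on procedures (Section 9.2), where the convention could be settled. This stands as far as it goes: the tables are reconcilable. But the protocol does not require that reading, and a 20-second test remains an explicitly permitted one.

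It also stands that the reach is narrow. Reported adverse events, which start at moderate severity, are untouched. For the any-AE outcome, Section 7.2.3 itself says that mild symptoms are common and hard to tell from malaria, so a lone Grade 1 Romberg change may fall in a patient already counted.

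A reader might infer more: that spurious neurologic events will occur, that they raise the incidence of neurologic adverse events, or that a sizeable error rate can be attached. The documents do not support this. A false event needs a patient in the window and a short test followed by a longer one, while early stopping hides true findings, so the net direction is open. Any probability for a hypothetical patient with constant endurance and randomly varying test lengths rests on assumptions that the protocol does not supply. Constant endurance is itself doubtful when Day 0 falls during acute malaria and later exams follow treatment. Nor is there ground to infer bias between arms: under Section 4.4 those who assess outcomes are blinded to treatment.

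**Conclusion.** The mismatch is real and minor. As written, Table A permits a test that cannot determine the Grade 1 criterion of Table B, and for patients who would lose balance between 20 and 30 seconds the recorded grade can depend on the examiner's stop time. The result can be a spurious new mild adverse event or a missed true one, confined to Grade 1, to patients over 4 years, and to the three-arm study.

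The effect is mainly noise in one sign and, through it, in the any-AE outcome. Its size cannot be computed from the protocol. This conclusion assumes that examiners use the permitted range and enter a still-standing patient as 0 when the test stops early. If all examiners already run to 30 seconds, nothing changes in practice and only the wording needs repair.

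**What to change.** Reconcile the two tables in Appendix 6: in Table A, replace the range for the eyes-closed Romberg stand with a timed 30 seconds at every visit, so that it matches the Grade 1 limit in Table B, and say so in examiner training. A test in which the patient loses balance ends at that moment, as it would now.

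The cost is one phrase in the appendix, a line in training, and at most 30 − 20 = 10 more seconds per exam, or 5 × 10 = 50 seconds per patient over the five scheduled exams. Recording the seconds stood is optional. It would need a new field, because the three-arm record form has a single grade cell per visit, and the correction does not depend on it.
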